# Discontinuing statins or not in the elderly? Study protocol for a randomized controlled trial

**DOI:** 10.1186/s13063-020-04259-5

**Published:** 2020-04-19

**Keywords:** Primary prevention, Statins, Elderly patients, Cost-effectiveness analysis, Randomized controlled trial, Mortality

## Abstract

**Background:**

The risk/benefit ratio of using statins for primary prevention of cardiovascular (CV) events in elderly people has not been established. The main objectives of the present study are to assess the cost-effectiveness of statin cessation and to examine the non-inferiority of statin cessation in terms of mortality in patients aged 75 years and over, treated with statins for primary prevention of CV events.

**Methods:**

The “Statins in the elderly” (SITE) study is an ongoing 3-year follow-up, open-label comparative multi-centre, randomized clinical trial that is being conducted in two parallel groups in outpatient primary care offices. Participants meeting the following criteria are included: people aged 75 years and older being treated with statins as primary prevention for CV events, who provide informed consent. After randomization, patients in the statin-cessation strategy are instructed to withdraw their treatment. In the comparison strategy, patients continue their statin treatment at the usual dosage. The cost-effectiveness of the statin-cessation strategy compared to continuing statins will be estimated through the incremental cost per quality-adjusted life years (QALYs) gained at 36 months, from the perspective of the French healthcare system. Overall mortality will be the primary clinical endpoint. We assumed that the mortality rate at 3 years will be 15%. The sample size was computed to achieve 90% power in showing the non-inferiority of statin cessation, assuming a non-inferiority margin of 5% of the between-group difference in overall mortality. In total, the SITE study will include 2430 individuals.

**Discussion:**

There is some debate on the value of statins in people over 75 years old, especially for primary prevention of CV events, due to a lack of evidence of their efficacy in this population, potential compliance-related events, drug-drug interactions and side effects that could impair quality of life. Data from clinical trials guide the initiation of medication therapy for primary or secondary prevention of CV disease but do not define the timing, safety, or risks of discontinuing the agents. The SITE study is one of the first to examine whether treatment cessation is a cost-effective and a safe strategy in people of 75 years and over, formerly treated with statins.

**Trial registration:**

ClinicalTrials.gov: NCT02547883. Registered on 11 September 2015.

## Background

Cardiovascular (CV) events, including ischaemic heart disease and cerebrovascular diseases, are the leading cause of death worldwide and are a major cause of morbidity in industrialised and developing countries [1]. CV events are multifactorial, and their prevention is defined as a coordinated set of actions, at the population or individual level, intended to eliminate or minimise the impact of CV diseases and related disabilities.

According to the “2016 European Guidelines on Cardiovascular Disease Prevention in Clinical Practice”, total CV risk estimation based on a risk estimation system such as the Systematic Coronary Risk Evaluation (SCORE), which estimates the 10-year risk of fatal cardiovascular disease (CVD), is recommended for adults > 40 years old [2]. People are categorised as being at high risk (familial hypercholesterolaemia, blood pressure > 180/110, diabetes mellitus without organ damage, or moderate chronic kidney disease (CKD); glomerular filtration rate (GFR) 30–59 mL/min/1.73 m2)” and “calculated SCORE between 5% and 10%) or very high risk (documented CV disease, diabetes mellitus with target organ damage, severe CKD (GFR < 30 mL/min/1.73 m2), calculated SCORE ≥ 10%) for CV events”.

The 2019 American College of Cardiology (ACC) and American Heart Association (AHA) Guidelines on the Primary Prevention of Cardiovascular Disease also recommend that adults aged 40–75 years who are being evaluated for CV disease prevention undergo 10-year estimation of risk of atherosclerotic CVD [3].

Among the possible interventions to reduce CV risk, statins are recommended for secondary prevention in all patients with CVD and for primary prevention in patients with elevated low-density lipoprotein cholesterol (≥ 190 mg/dL) or with diabetes mellitus, and those determined to be at sufficient CV risk (high risk and very high risk) after a clinician–patient discussion of risk.

Statins are inhibitors of hydroxymethylglutaryl-CoA reductase and thus reduce the synthesis of cholesterol, especially low-density lipoprotein (LDL) cholesterol, an independent risk factor for CV events. Numerous large-scale randomized studies over the last 20 years have demonstrated the effectiveness of statins for reducing CV risk in primary and secondary prevention [4]. However, information on patients over 75 years old is lacking, as no randomized trials have been conducted in this population.

The European Guidelines and the 2019 ACC/AHA Guideline acknowledge that special considerations are required when prescribing lipid-lowering agents in older people because exposure to higher doses (or higher potency) may not increase life expectancy but may increase the risk of adverse effects. Assessment of risk status and a clinician–patient discussion of risk are needed to decide whether to initiate or continue statin treatment.

Statins represent one of the largest pharmaceutical industry markets in France; in 2014, around 5 million people were treated with statins, representing a total cost of 550 million euros. People 75 years and older represented 9.3% of the total population in 2019 [5]. We estimate that around 25% of these people are treated with statins, including around 40% in the context of primary prevention (target population over 500,000 people in France).

Given the absence of formal evidence of efficacy, and the high level of side effects, the risk/benefit ratio of primary prevention with statins in elderly patients has not been established. With no controlled studies to validate the benefits of statins in this population, there is some controversy in the literature about their use in this age group [6–16].

One previous trial implied that stopping statin medication therapy is safe and may be associated with a number of benefits, including improved quality of life (QOL) among patients with advanced life-limiting illness [17].

We postulate that statin cessation in patients older than 75 years, when prescribed for primary prevention of CV events, will be safe and may improve QOL through the absence of adverse effects, and lower the costs for the French National Health Insurance System.

The two main objectives of this study are therefore to assess the cost-effectiveness, in real-life use, of statin cessation in patients over 75 years old being treated for primary prevention of CV events and to examine the non-inferiority of statin cessation in terms of all-cause mortality in patients older than 75 years.

## Methods/design

### Trial design and settings

The Statins in the elderly (SITE) study is a 3-year follow-up, open-label, comparative multi-centre randomized clinical trial being conducted in two parallel groups in outpatient primary care offices. Our objective is to conduct a randomized controlled trial that is representative of usual care conditions. Our study is being conducted in general practices in France, and the eligibility criteria are limited, apart from regulatory requirements, to age and treatment with statins for the purpose of primary prevention.

All general practitioners (GPs) working in primary care centres in France can enrol patients in the study. They need only to use informatics devices to complete the electronic case report forms (e-CRF) during patient follow up.

### Eligibility criteria

The study population consists of patients aged 75 years and over who have no history of CV disease and who are being treated with a statin and regularly visiting their referent GP in France. Participants meeting the following criteria are eligible for inclusion: people aged 75 years and older who have been treated with statins for at least 1 year for primary prevention of CV events, and who give informed consent. Patients with hypertension and/or diabetes mellitus may be included.

Participants meeting any of the following criteria are excluded: progressive morbid disease and life expectancy of 3 months or less, diagnosed with dementia, suffering from known homozygous or double heterozygous familial hypercholesterolaemia, or unable to provide informed consent.

### Intervention

In the statin cessation strategy, the statins are stopped and patients are asked to end their treatment on the day of randomization. In the comparison strategy, patients continue their statin treatment at the usual dosage. Compliance with the use of statins is assessed by the Morisky questionnaire at each visit.

### Randomization

Randomization is being carried out centrally using the e-CRF on the day of the visit for participant inclusion, after the participant has signed the consent form. Participants are considered enrolled in the trial when randomized.

The randomization is unbalanced, with a 5:4 ratio in favour of the statin-continuation group to take into account a 20% risk that patients allocated to the statin continuation group will stop statins after randomization for any reason (side effects, patient’s decision, physician’s decision). The allocation sequence was elaborated using computer-generated random numbers, and was not stratified. To reduce predictability of a random sequence, we used blocks of varying size. A document describing the randomization procedure is kept confidential within the Clinical Epidemiology Unit.

Taking statins or discontinuing statins will not require alteration to usual care pathways (including use of any medication) and these will continue in both trial arms. Participants in the statin discontinuation group who experience a new vascular event will be allowed to restart statins at the discretion of the investigator and according to good clinical practice.

### Outcome measures

#### Economic endpoints

The cost-effectiveness of the statin cessation strategy compared to continuation of statins will be estimated based on the incremental cost per quality-adjusted life year (QALY) gained at 36 months, from the perspective of the French healthcare system. QALYs will be measured using the Euro-QOL five-dimension, three-level (EQ-5D-3 L) questionnaire at inclusion and at each follow-up visit [18]. This questionnaire has been validated in the French population.

Healthcare resources and costs will be extracted from the French Administrative Health Care Database (Système National des Données de Santé, SNDS) by a merging procedure, operated by the French National Health Insurance Fund and using data from the SITE trial. The SNDS gathers all reimbursement data for 98.8% of the French population [19]. The time horizon of the study (36 months) implies a discounting of costs and outcomes. In accordance with the methodological economic guidelines of the French National Health Authority (Haute Autorité de Santé, HAS), we will apply a 4% discount rate.

Following cost-effectiveness analysis (CEA), budget impact analysis (BIA) will provide useful information about the sustainability of the statin cessation strategy if it were applied to the entire French healthcare system. It will consider outpatient costs, hospital costs, medical and non-medical costs induced or avoided by stopping statins, and all budgetary implications related to changes in health management and/or health status improvement. The difference between induced and avoided costs will provide the net benefit to the healthcare system of widespread adoption of the statin cessation strategy for primary prevention among elderly individuals in France.

#### Main clinical endpoint

Overall mortality will be the primary clinical endpoint. As the investigators are GPs, they are informed of the death of their patients and will therefore constitute the source of mortality data in this trial.

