### Amendment

To extend inclusions, the protocol was amended in March 2019 to also include patients from hospital departments.

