Our study will have some limitations. First, we acknowledge that this is a pragmatic trial without blinding. The study participants and their physicians will know whether statin therapy has been continued or discontinued. The choice was to evaluate a strategy of discontinuing statins rather than to evaluate statin prescriptions alone. In theory, the absence of blinding could lead to a measurement bias due to greater surveillance of CV events in the discontinuation group. This will be closely monitored through the data from the SNDS. In addition, this is why the total mortality rate was chosen as our primary endpoint. Second, patients with previous dementia cannot be included in the trial, so our results will not be generalizable to this population. Third, although our sample is quite large, we cannot exclude a tendency from the investigators to recruit people with very few CV risk factors rather than patients with advanced disease and poor outcomes. Particularly, the inclusion of patients with diabetes mellitus will be monitored. Finally, patients treated with statins are being included in the SITE trial regardless of the specific type of statin. Therefore, we will not be able to examine specific treatments or dosages. However, we believe that the SITE study will be one of the first to show that a strategy of treatment cessation is cost-effective and does not adversely affect the prognosis of people over 75 years of age who are treated with statins.

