## Trial status

Patient recruitment started on 15 June 2016. The expected recruitment completion date is 31 December 2019.

The protocol version number is 8.0, dated 5 June 2019.

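### The stated reason for taking deaths from investigators alone, that they are GPs, no longer covers every patient since hospital departments were added, and no second source of vital status is named

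*Protocol article*

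**What the plan says.** Under Main clinical endpoint the article states: "Overall mortality will be the primary clinical endpoint". It then names the source and the reason for it: "As the investigators are GPs, they are informed of the death of their patients and will therefore constitute the source of mortality data". No second source is given there or elsewhere.

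Under Amendment it reports that "the protocol was amended in March 2019 to also include patients from hospital departments". Trial status says: "The protocol version number is 8.0, dated 5 June 2019". The version described therefore postdates the amendment, and both statements are current text.

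A linkage to the French administrative health database (SNDS) is planned, with two stated uses. Economic endpoints says: "Healthcare resources and costs will be extracted from the French Administrative Health Care Database", and adds: "The SNDS gathers all reimbursement data for 98.8% of the French population". The Discussion, on possible closer surveillance of cardiovascular events in the discontinuation group, says: "This will be closely monitored through the data from the SNDS". Neither use is the ascertainment of death.

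Statistical methodology sets missing outcomes to failure, with failure meaning death, in the non-inferiority analysis.

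**The concern.** The primary endpoint has one named source, and that source is justified by a fact about the investigators that ceased to be true of all patients in March 2019. For a patient recruited in a hospital department, the article gives no ground for assuming that the investigator learns of a death up to three years later.

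This matters more here than in many trials because of the missing-data rule. A patient whose status is unknown is not set aside but enters the primary analysis as a death. Unknown status spread evenly over the arms raises both rates, which widens the interval, and pulls a true difference towards zero. Unknown status spread unevenly shifts the estimated difference directly. The Discussion relies on total mortality as protection against bias in an open-label trial. That protection depends on vital status being known equally well in both arms.

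**Working it through.** **Inputs from the article.** Three-year mortality 15% in both groups, margin 5 percentage points, one-sided alpha 2.5%, power 90%, 1080 cessation and 1350 continuation (Sample size). Missing counts as death, and the primary analysis excludes patients not treated as planned (Statistical methodology).

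**Assumed inputs.** The article gives no share of patients with unknown vital status and no number recruited in hospitals. All unknown shares below are illustrations.

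**Step 1: reproduce the plan.** With unpooled variance and equal arms,

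n = 2 × 0.15 × 0.85 × (1.960 + 1.282)² / 0.05² ≈ 1072 per arm,

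close to the stated 1080. Allowing for 20% stopping, 1080 / 0.80 = 1350, so the total is 2430. At 1080 v 1080 the standard error is √(2 × 0.15 × 0.85 / 1080) = 0.01537, and power is Φ(0.05/0.01537 − 1.960) = Φ(1.294) = 90.2%. The sample size is sound, and this point does not affect it.

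**Step 2: equal unknown share u in both arms, no true difference.** The analysed rate is p = 0.15 + 0.85u.

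| u (assumed) | Analysed mortality | Power, 1080 v 1080 | Power, 1350 v 1080 |
|---|---|---|---|
| 0% | 15.0% | 90.2% | 92.9% |
| 2% | 16.7% | 87.6% | 90.7% |
| 4% | 18.4% | 85.1% | 88.5% |
| 10% | 23.5% | 78.2% | 82.3% |

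The 2% row would arise, for example, if 10% of patients came from hospitals and 20% of those had unknown status (0.10 × 0.20). The 4% row would need 20% from hospitals (0.20 × 0.20).

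**Step 3: unequal unknown shares.** With equal true mortality of 15%, the spurious difference is 0.85 × (u in cessation − u in continuation). Each point of imbalance therefore moves the estimate by 0.85 points, and 0.85 / 5 = 17% of the margin.

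- 2% continuation v 3% cessation: shift +0.85 points, power 72.6%.
- 3% continuation v 5% cessation: shift +1.7 points, power 50.8%.

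**Step 4: the unsafe direction.** Let true mortality lie at the margin, 15% continuation v 20% cessation. The analysed rates are 0.15 + 0.85u and 0.20 + 0.80u.

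- 10% unknown in both arms: 23.5% v 28.0%. The difference shrinks to 4.5 points and one-sided type I error is 4.5% instead of 2.5%.
- 3% continuation v 2% cessation: 17.55% v 21.6%. The difference is 4.05 points and type I error is 8.0%.

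The power and error figures in steps 3 and 4 use 1080 v 1080.

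**The case against.** The strongest reply is that no loss of deaths has been shown, and this stands. The article does not say who follows patients recruited in hospital. Their own GP may do so, since Eligibility criteria still describes patients who regularly visit a referent GP. Follow-up is also active. Table 1 schedules visits at 3, 12, 24 and 36 months, serious adverse events are reported at once, annual safety reviews look at all-cause mortality, and monitoring includes telephone contact and a site visit after the last follow-up.

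A reader might infer that deaths are better known in the continuation arm because those patients return for statin prescriptions. The article does not support this. Visits and adverse-event reporting are the same in both arms, usual care continues in both, and the only asymmetry the article itself raises is closer cardiovascular surveillance in the discontinuation group. A reader might also point to patients who change practice or move into care. That is plausible, but no rate is given.

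The illustrative shares are also open to challenge. Recruitment was to run from 15 June 2016 to 31 December 2019, about 42.5 months, with hospitals eligible for at most about 10. If accrual was even, a 20% hospital share would need about 0.20 / (10/42.5) = 85% of later recruits to come from hospitals, so the 4% row is a stretch on that route. With all 1350 v 1080 patients analysed, power at 2% unknown is still 90.7%.

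Finally, a condensed article may leave follow-up logistics to the full protocol. That answers a complaint about missing detail. It does not answer this one: the article positively states one source and one reason, and the reason conflicts with its own amendment.

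**Conclusion.** The point holds as an inconsistency in how the primary endpoint is sourced. The reason given for relying on investigators does not cover hospital-recruited patients, no alternative source is named, and unknown status becomes death.

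Actual loss of deaths and any imbalance between arms are not demonstrated. What the arithmetic shows is sensitivity. A small, balanced unknown share costs little: 2.6 points of power at 2% unknown (90.2 − 87.6). A small imbalance costs much more, at about 0.85 points of mortality difference per point, and can work for or against non-inferiority. These figures rest on assumed unknown shares, 15% mortality and 1080 patients per arm.

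It would also go too far to say that every participant is already linked to a death register. The article plans a merge for resources and costs. The 98.8% is coverage of the French population, not success of linkage, and the database is described as holding reimbursement data, with no mention of vital status. The change is worth making because it is cheap and protects the primary endpoint.

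**What to change.** Reword Main clinical endpoint so that it no longer rests on every investigator being a GP. Keep investigator reports as a source. Add a cross-check of vital status at 36 months against the SNDS merge already planned under Economic endpoints, for all randomized patients whose consent allows it, including withdrawn patients who agreed to the use of their data. Apply it identically to GP- and hospital-recruited patients and to both arms. Count missing as death only where status is still unknown after both sources.

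First confirm whether the SNDS extraction can supply date of death. If it cannot, a date of care delivered after month 36 shows that the patient was alive at that point. A payment date does not, because a reimbursement can follow death for earlier care. The absence of later care proves nothing.

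The cost is a change of wording and some extra variables in an extraction already planned, subject to data access. The primary result would wait for that extraction, and the linkage may not reach every participant, so investigator reports remain necessary. The planned sample size does not change.

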#### Secondary endpoints

The secondary endpoints are:
QOL score measured by the Quality of Life Scale SF12, which has been validated in older peopleIncidence of CV eventsIncidence of non-CV events (diabetes mellitus and cognitive disorders)

### Timeline and recruitment

This study employs the research network of French universities’ primary care departments (PCDs). Each PCD appoints a coordinating physician by geographic area to mobilise investigating physicians (486 expected in the study).

The recruitment of GPs all across France maximises representativeness and limits the impact of potential local practices. The representativeness of the investigators is being documented by collecting data about their sociodemographic profiles, activity, and training.

Patients are being recruited through consultations over a period of 36 months. Eligible patients not included in the study are being reported, along with the reason for non-inclusion.

### Conduct of research

Patients are approached and screened by GPs during their usual medical visit or on the renewal of their medication. Patients are first pre-included with their referent GP, and then after a time of reflection (that may be few minutes to days or months until the next visit), they sign the consent form with the GP and are randomized to one of the two strategies. On the consent form, participants are asked if they agree to use of their data should they choose to withdraw from the trial. Participants are also asked for permission for the research team to share relevant data with people from the Universities taking part in the research or from regulatory authorities, where relevant. This trial does not involve collecting biological specimens for storage. Table 1 outlines the different phases of the study and data collection.

**Table 1 Tab1:** Design of the SITE study

Timepoint	Study period					
	Pre-inclusion T − 1	Inclusion T 0	M3 *+/−* 1 month	M12 +/− 3 months	M24 +/− 3 months	Close-out M36 +/− 3 months
